### Analysis plan

#### Demographic data and behavioral tasks analysis

All behavioral data will be analyzed using the statistical software IBM SPSS Statistics. For the analysis a two-way factorial ANOVA will be used. More precisely for the 3-back task response accuracy will be recorded and two-way ANOVAs will be used for comparisons between groups. For the facial recognition paradigm, the number of correct responses will be recorded and two-way factorial ANOVAs will be used for between groups comparisons. For the coin rotation task, the number of 180° coin rotations in 10 s will be recorded and two-way factorial ANOVAs will be used for comparisons between groups.

The probabilistic learning task will be analyzed using the Hierarchical Gaussian Filter (HGF) model to infer participants’ individual belief trajectories concerning the cards and the social cues. Model comparisons will be carried out by means of Bayesian Model Selection. Group-specific differences in model parameters will be evaluated by means of mixed ANOVAs with schedule stability as a within-subject factor, information type as the within participant factor (social vs. card). Groups and brain stimulation will be the between subject factors.

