### Objectives

To optimally probe the effects of rTMS in the rTPJ in ASD, we will combine the afore mentioned state-of-the-art stimulation techniques, including individualized fMRI-guided targets, time-efficient intermittent theta-burst-stimulation (iTBS) and a stereotactic neuronavigation.

In our study on the basis of the current literature the neurocognitive pathway of mentalizing will be localized using a well-established video-based fMRI task, which contrasts brain activation during scenes with socially engaging vis-a-vis socially neutral content [39]. This has been shown to consistently localize activation maxima in regions involved in social cognition including the dmPFC and TPJ on the single-subject level [39]. In a second session, each participant’s activation maximum in the rTPJ will be used as a stimulation target to conduct a neuronavigated iTBS intervention with the aim of modulating social information processing. The effects of the stimulation will be measured by using a test battery encompassing social cognitive as well as cognitive control tasks.

We hypothesize that adults with ASD without intellectual impairment will show an iTBS-induced improvement in social information processing, measured by an established probabilistic learning task that requires the integration of both social and non-social information [40]. In particular, participants with ASD without intellectual impairment belonging to the treatment group will show an increased ability to integrate social information into their decision-making process compared to the control group. We hypothesize that these effects are not due to changes or baseline differences in executive functioning.

Secondary analyses will investigate group differences in executive function tests as well as brain activation and connectivity in the ASD and control group.

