### Sample size calculation

A power analysis with an estimated effect size of 0.3, a power of 0.8 and an alpha error of 0.05 was used to determine the required sample size for this study using G* Power [41]. Based on this analysis 90 participants are required. In order to divide the participants in four groups a total sample of 92 participants is required. Taking possible drop-outs as well as loss of data due to technical problems into account we have decided to include 52 participants in each arm of the study, i.e. 52 participants with ASD and 52 participants without ASD. Only little prior evidence exists in the field of neuronavigated TMS in adults with ASD, so that no prior studies could serve as a basis for the power analysis. Since this is a proof-of-concept study we opted for a small effect size, so that even smaller effects of the intervention can be detected.

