### Inclusion/exclusion criteria

Participants with an already confirmed ASD diagnosis will be included if they: (1) are 18 to 65 years of age, (2) have not a contraindication for an MRI scan, (3) have an AQ-score equal to or greater than 28, (4) have an IQ greater than 80 and (5) have a BDI II score less than 20. Healthy controls with no history of psychiatric disorders and no psychiatric symptoms as assessed by an experienced consultant psychiatrist during the screening interview will be included if they: (1) are 18 to 65 years old, (2) have not a contraindication for an MRI scan, (3) have an AQ-score equal to or less than 27, (4) have an IQ greater than 80 and (5) have a BDI II score less than 20.

General exclusion criteria will be: (1) known epilepsy, (2) intracranial metallic foreign bodies, intracranial implants and big head tattoos, (3) significant brain malformations, brain tumors, cerebrovascular events (strokes), traumatic brain injuries, neurodegenerative diseases and brain surgeries, (4) implanted cardiac pacemaker, (5) severe illness, (6) tinnitus, (7) glaucoma, (8) pregnancy, (9) medication affecting the seizure threshold, (10) claustrophobia, 11) current or previous treatment with Deep Brain Stimulation or Vagus nerve Stimulation, 12) heavy alcohol consumption (> 60 g alcohol per day) or substance abuse, 13) limited knowledge of German language.

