### Experimental procedure

An overview of the study plan is depicted in Fig. 1. At the beginning, all participants will undergo a screening session conducted by an experienced psychiatrist so that inclusion/exclusion criteria can be assessed and necessary information can be reviewed. Afterwards informed consent will be obtained and as a part of the screening the medical history will be taken, the Autism Spectrum Quotient (AQ), the Intelligence Quotient (IQ) measured using the multiple-choice vocabulary intelligence test MWT, the Beck Depression Inventory (BDI II) score, the Edinburgh handedness inventory score, as well as sociodemographic data will be collected [42–45]. The data from the screening session will be used in secondary analysis. Participants will be randomly assigned to one of the two stimulation conditions, i.e. verum-iTBS or sham-iTBS. The entire sample will therefore include four groups (ASD individuals receiving verum-iTBS, ASD individuals receiving sham-iTBS, controls receiving verum-iTBS and controls receiving sham-iTBS). All participants will receive an anatomical MRI scan, including a T1-weighted sequence as well as an fMRI scan. During the fMRI scan a well-established video-based social perception task (social localizer) will be administered [39]. In this paradigm audiovisual movie clips displaying pre-selected social clues are presented in order to detect the brain networks subserving perception. Based on this localizer, activation maxima in rTPJ will be extracted at the single-subject level, which will be then used as personalized targets for the neuronavigated iTBS session. Coil positions will be navigated using a frameless stereotaxic neuronavigation system (Localite GmbH). This allows to co-register T1 images of the participants with their anatomical landmarks, enhancing the precision of the stimulation over the fMRI-derived activation peaks of the rTPJ. For the iTBS the following protocol will be used: 600 pulses will be given in 1,84 s trains repeated every 10 s for a total of 189 s at an intensity of 70% of the motor threshold. Stimulations will be performed with a PowerMAG Research 100 stimulator (MAG and More GmbH) and a PMD70-aCool coil (verum-iTBS) as well as a PMD70-aCool-Sham coil (sham-iTBS). Directly after stimulation, the following tasks will be administered in the following order: (1) probabilistic learning task, (2) a facial recognition paradigm, (3) coin rotation task and (4) 3-back task [40, 46–48]. The estimated time required to complete these tasks is approximately 35–40 min. The time of completion of the TMS, as well as the start times of each task, will be recorded. There will be a maximum of 5 min between the completion of the TMS and the start of the social probabilistic learning task. As a result, all tasks will be completed within approximately 40–45 min after the completion of the TMS.

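### The three tasks run only after stimulation are analysed without covariates, although age and IQ are available from screening: verum versus sham stays valid but loses precision, and the ASD-versus-control effect is open to confounding

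*Protocol article*

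**What the plan says.** Under Demographic data and behavioral tasks analysis, the protocol article states "For the analysis a two-way factorial ANOVA will be used". It then repeats this model separately for the 3-back, the facial recognition paradigm and the coin rotation task. No covariate is named for any of them.

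Under Experimental procedure, only the social learning task is run both before and after stimulation, so these three tasks have no pre-stimulation score. The same section collects MWT IQ, BDI-II, AQ, handedness and sociodemographic data at screening and says of them: "The data from the screening session will be used in secondary analysis". How they will be used is not stated.

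Under Inclusion/exclusion criteria, ASD participants qualify if they "are 18 to 65 years of age" with an IQ above 80. Controls have the same age range and IQ floor. No matching of controls to ASD participants is described. Study design and ethics approval randomises stimulation (verum or sham); diagnosis cannot be randomised.

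Under Objectives: "Secondary analyses will investigate group differences in executive function tests as well as brain activation and connectivity in the ASD and control group".

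**The concern.** With no baseline score in the model, everything that makes one person better than another at these tasks stays in the error term. Entry is open to nearly five decades of age and any IQ above 80, so part of that spread may be predictable from data already in hand. Leaving it out costs precision in the verum-sham comparison. For facial recognition, the article predicts a benefit of verum over sham within the ASD group, a contrast that uses only half the sample. For the 3-back and coin rotation it predicts no improvement, and an imprecise test makes an absence of difference easier to find.

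The ASD-versus-control comparison raises a different issue. Diagnosis is observed, and ASD participants are additionally recruited through a specialist clinic. If the groups differ in age or IQ, the unadjusted diagnosis main effect mixes that difference with the effect of diagnosis. The executive-function comparison in the Objectives is where this would matter.

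**Working it through.** **1. The plan's own figure.** Inputs from Sample size calculation: "A power analysis with an estimated effect size of 0.3, a power of 0.8 and an alpha error of 0.05"; "Based on this analysis 90 participants are required"; "In order to divide the participants in four groups a total sample of 92 participants is required"; and, with an allowance for losses, "we have decided to include 52 participants in each arm of the study", that is 52 + 52 = 104.

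Read 0.3 as Cohen's f for a 1-df effect in a four-cell ANOVA without covariates. The noncentrality is λ = f²N, with denominator df = N − 4.
- N = 89: power 0.799. N = 90: power 0.803. The stated 90 reproduces exactly.
- N = 92: 0.812. N = 104: 0.858.

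The sample size therefore agrees with an unadjusted 1-df ANOVA on the whole sample.

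**2. Precision of verum versus sham within ASD.** Assumptions: 1:1 allocation, so 104/4 = 26 per cell; difference d = 2f = 0.6 SD; two-sided α = 0.05; error variance pooled over the four cells. R² is the share of outcome variance explained by age and IQ. The article gives no value, so a range is shown.

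Noncentrality δ = [0.6/√(1 − R²)] × √(26/2); df = 100 unadjusted, 98 with two covariates.

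| R² (assumed) | SE ratio √(1 − R²) | δ | Power |
|---|---|---|---|
| none, unadjusted | 1.000 | 2.163 | 0.572 |
| 0, adjusted | 1.000 | 2.163 | 0.572 |
| 0.05 | 0.975 | 2.220 | 0.594 |
| 0.10 | 0.949 | 2.280 | 0.617 |
| 0.20 | 0.894 | 2.419 | 0.668 |
| 0.30 | 0.837 | 2.586 | 0.726 |

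Using the error variance of the ASD cells alone gives 0.564 unadjusted and 0.608, 0.659 and 0.717 for R² = 0.10, 0.20 and 0.30. A third covariate (df = 97) changes none of the pooled figures by more than 0.001. The gain is equivalent to a sample larger by a factor 1/(1 − R²): 1.05, 1.11, 1.25 and 1.43.

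**3. A 1-df effect on the whole sample.** With λ = f²N/(1 − R²) and df = N − 6, power at N = 104 is 0.858 unadjusted and 0.875, 0.891, 0.923 and 0.952 for R² = 0.05, 0.10, 0.20 and 0.30. At N = 92 with R² = 0 it stays at 0.812, so useless covariates cost almost nothing.

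**4. Confounding of the diagnosis main effect.** Bias in SD units = (covariate-outcome correlation) × (ASD-control imbalance in SD). Both factors are assumed. With no true diagnosis effect, the rejection rate follows from λ = (bias/2)² × 104 on 1 and 100 df.

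| Correlation | Imbalance (SD) | Bias (SD) | Rejection rate |
|---|---|---|---|
| any | 0 | 0 | 5% |
| 0.2 | 0.4 | 0.08 | 6.9% |
| 0.3 | 0.4 | 0.12 | 9.3% |
| 0.5 | 0.4 | 0.20 | 17.3% |

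**5. Which effects are touched.** In 20,000 simulated trials with 26 per cell, an ASD-control imbalance of 0.4 SD and a slope of 0.4, the unadjusted diagnosis effect was biased by 0.16 SD and rejected in 12.9%. The stimulation main effect and the interaction had mean estimates of 0.000 and 0.004, each rejected in 5.0%. The simulation has no effect modification by the covariate.

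**The case against.** A covariate list is usually a matter for the SAP, which is not shown. The article reserves the screening data for secondary analysis, and the ASD-control executive-function comparison is itself secondary, so adjustment is unspecified rather than excluded. Unadjusted ANOVA is valid under randomisation and matches the sample-size calculation. Every gain above rests on an R², and every bias on an imbalance, that the article does not give. The learning task that carries the main hypothesis has a baseline run and its own mixed ANOVA.

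Most of this stands, and it limits the point. It does not remove it: the article goes beyond silence by writing out the model task by task, and an analyst following that text would fit no covariate.

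A reader might infer three stronger things, none of which the documents support.
- That the planned ANOVA confounds the results generally. Only the diagnosis main effect is exposed, and only if the groups actually differ. The stimulation effect is randomised and unbiased, and so is the interaction unless the covariate modifies the stimulation effect.
- That controls are known to be unmatched. The article does not say whether they are matched.
- That adjusting for IQ gives the correct diagnosis comparison. It reduces confounding without removing it, and comparing cognitive performance at equal vocabulary IQ is a different question from comparing it overall.

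**Conclusion.** The point holds as a missed and nearly free improvement, not as an error in the plan. For verum versus sham on the three tasks, the unadjusted analysis is valid. Adjustment would raise power for a 0.6 SD within-ASD difference from about 57% to between 59% and 73% if R² lies between 0.05 and 0.30, with no gain and negligible loss if R² is near zero. This assumes 26 per cell and full follow-up.

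The ASD-versus-control main effect is open to confounding by age or IQ. In the examples worked, biases of 0.12 to 0.20 SD raise the false-positive rate from 5% to about 9% to 17% at N = 104; with no imbalance in age or IQ there is no bias from them. Severity is minor to moderate, because only secondary and control tasks are affected.

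**What to change.** For facial recognition, 3-back and coin rotation, pre-specify the diagnosis-by-stimulation model with age and MWT IQ as covariates, plus sex if it is among the recorded sociodemographic data. Keep the unadjusted two-way ANOVA as sensitivity analysis. Do not adjust for AQ, since AQ cut-offs form part of the group definition.

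Label ASD-control differences observational. Report them adjusted for age (and sex) both with and without IQ, and say which question each version answers. If controls are in fact matched, state on which variables.

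The cost is a few sentences and two or three degrees of freedom out of 100. No new data are needed, subject to confirming that sex is recorded. The change should be made before any outcome data are examined, so that covariates are not chosen after an imbalance is seen.

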
**Fig. 1 Fig1:**
[figure not shown]
Study flow diagram

The social learning task, which will be used to measure changes in social cognition, is the only task, which will be administered before and after brain stimulation.

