(b) The social probabilistic learning task will be administered before and after iTBS [40]. In this task, participants have to integrate social and non-social information to learn which one of two cards leads to a reward. The winning probability of each card will change several times during the experiment, as will the helpfulness of the social cue. The participants will not be explicitly told to use social information. When selecting the winning card on a given trial, the number of points depicted on the card can be won. For the analysis, the main behavioural outcomes are the number of correct responses, the total score accumulated and the number of trials where participants considered social information. In addition, a hierarchical Gaussian filter model will be used to mathematically model how beliefs about the helpfulness of the social cues are learned and integrated with non-social beliefs about the probability of reward for each stimulus. Previous studies using dynamic learning tasks in conjunction with computational modeling have shown that high in autistic trait individuals find it difficult to integrate social and non-social cues and to form predictions about volatile environments [49, 50]. We hypothesize that ASD individuals receiving verum-iTBS compared to control treatment will demonstrate an increase in the number of correct responses and in the proportion of trial where they follow social cues. With computational modelling, we aim to examine the underlying cognitive mechanisms that bring about these behavioral outcomes. We hypothesize that iTBS will improve the ability to integrate social and non-social information, as measured by a social weighting parameter, while not having an effect on how participants update beliefs in the non-social domain.

(c) The 3-back task will be used as a control task to measure a domain of the executive functions by testing participants’ working memory and memory capacity [46]. Participants will be presented with a series of alternating stimuli (numbers) changing in random sequence, eventually repeating and will be asked to report when a stimulus matches another stimulus presented three trials back (*N* = 3). The number of correct responses and reaction time will be counted. No improvement in participants´ executive function ability after neuronavigated iTBS is anticipated.

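### The social learning task is run before and after iTBS, but its stated model has no time factor, change score or baseline covariate and does not say which run is analysed

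*Protocol article*

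**What the plan says.** On design, the Outcome measures section, item (b), states: "The social probabilistic learning task will be administered before and after iTBS". The text under Fig. 1 gives the purpose, "The social learning task, which will be used to measure changes in social cognition", and adds that it "is the only task, which will be administered before and after brain stimulation". Under Objectives, the main hypothesis is that adults with ASD "will show an iTBS-induced improvement in social information processing, measured by an established probabilistic learning task". Outcome measures (b) predicts that the ASD verum group, compared with control treatment, "will demonstrate an increase in the number of correct responses and in the proportion of trial where they follow social cues".

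On analysis, the section on demographic data and behavioural tasks fits a Hierarchical Gaussian Filter to this task and then compares model parameters by "mixed ANOVAs with schedule stability as a within-subject factor, information type as the within participant factor (social vs. card". It continues: "Groups and brain stimulation will be the between subject factors". The same section opens with a two-way factorial ANOVA for behavioural data in general, and the details that follow cover the 3-back, facial recognition and coin rotation tasks. Neither description mentions session, change or baseline.

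The Sample size calculation section uses an effect size of 0.3 (metric not named), power 0.8 and alpha 0.05. It arrives at 90, raises this to 92 for four groups, and plans to enrol 52 with ASD and 52 without.

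**The concern.** The pre/post design creates one repeated factor, and it is the one missing from a model whose factors are otherwise listed one by one. Neither listed within-subject factor can stand in for it. Information type is defined as social versus card. Schedule stability is not defined further, but the article describes card and cue probabilities as changing several times during the experiment, so it reads as a property within a run.

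The dependent variable is therefore left open for the task that carries the main hypothesis. It could be the post-stimulation parameter alone, a pre-to-post change, or parameters from both runs. These analyses differ in precision, and one of them attenuates the effect. Leaving the choice open also allows it to be made after the data are seen. The three behavioural outcomes of the task (correct responses, total score, trials using social information) have the same gap, and appear to be covered only by the general two-way ANOVA.

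**Working it through.** **1. The plan's own figure.** Take 0.3 as Cohen's f (an assumption). For a fixed-effects ANOVA effect with 1 numerator df and four cells, the noncentrality is λ = f²N. At N = 90, λ = 0.09 × 90 = 8.1 with 86 denominator df, and power is 0.803. The smallest N that reaches 80% is 90, which matches the article. This calculation contains no repeated measure, so the planned size does not draw on the pre-stimulation run either.

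**2. Candidate analyses.** Let r be the pre-post correlation, with equal variances and no expected baseline difference between arms (randomisation). For a post-stimulation effect of d SDs, the effective standardised effects are:

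- post-only: d
- post adjusted for pre: d / √(1 − r²)
- change score, or stimulation × time: d / √(2(1 − r))
- both runs averaged, no time term: (d/2) / √((1 + r)/2)

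In the last case the untreated run contributes nothing to the effect, which is why it is halved.

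**3. Within ASD, verum versus sham.** Inputs: 26 per cell (52 with ASD split equally between conditions), d = 0.6 (assumed; it equals 2f for f = 0.3), two-sided alpha 0.05, and error df pooled over four cells (100, or 99 with a covariate). The noncentrality is the effective effect × √(26/2). The article gives no r, so a range is shown.

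| Analysis | r = 0.3 | r = 0.5 | r = 0.7 |
|---|---|---|---|
| Post-only | 57% | 57% | 57% |
| Post adjusted for pre | 61% | 70% | 85% |
| Stimulation × time (change) | 44% | 57% | 79% |
| Both runs, no time term | 26% | 24% | 21% |

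Example at r = 0.5: the adjusted effect is 0.6/√0.75 = 0.693, and 0.693 × √13 = 2.50, giving 70%. The pooled effect is 0.3/√0.75 = 0.346, and 0.346 × √13 = 1.25, giving 24%.

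**4. Overall stimulation test on the plan's own terms.** With f = 0.3 and N = 92, λ is multiplied by 1/(1 − r²) for baseline adjustment (one extra df), 1/(2(1 − r)) for change, and 1/(2(1 + r)) for pooling.

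| Analysis | r = 0.3 | r = 0.5 | r = 0.7 |
|---|---|---|---|
| Post-only | 81% | 81% | 81% |
| Post adjusted for pre | 85% | 91% | 98% |
| Stimulation × time (change) | 67% | 81% | 96% |
| Both runs, no time term | 42% | 38% | 34% |

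**5. Ordering.** For r below 1, 1 − r² = (1 − r)(1 + r) is smaller than 2(1 − r), so baseline adjustment is more precise than change. Change beats post-only only when 2(1 − r) < 1, that is, r > 0.5.

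**The case against.** A reader might infer that the plan does not test the effect of iTBS at all. The article does not support that. Stimulation is randomised and sham-controlled, so a post-only comparison of verum with sham is an unbiased test without any baseline. The listed factors would also test stimulation-induced change if the dependent variable were a change score. The article's talk of measuring changes is compatible with that reading, although the analysis section does not state it.

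A reader might also infer that the two runs will be pooled and the effect halved. Nothing in the article says so. Those figures are a conditional worst case and cannot carry the severity.

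The size of the gain is uncertain too. The article gives no pre-post correlation, and the advantage over post-only within ASD runs from 4 percentage points at r = 0.3 to 28 at r = 0.7. The low post-only figure of 57% comes mainly from testing within ASD alone; the overall stimulation test has 81%. That gap is not caused by the missing time factor. The calculation with 26 per cell also makes no allowance for drop-out, whereas the stated requirement of 92 is 23 per cell.

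Finally, a condensed article may leave detail to a fuller document. That would answer simple silence. Here the article writes out the model's factors, and the list does not match the design it describes. That much of the point stands.

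**Conclusion.** The point holds as an incomplete and mismatched specification with an avoidable loss of precision. It is not a finding of bias or of an untested hypothesis. The article plans a baseline run for every participant and then states a model with no place for it, leaving the analysed quantity open.

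If the analysis is post-only, not using the baseline costs 4 to 28 percentage points of power within ASD (57% against 61% to 85%), or 4 to 17 points for the overall stimulation test at N = 92 (81% against 85% to 98%), for r from 0.3 to 0.7. These figures rest on the assumed correlations, an assumed 0.6 SD effect or f = 0.3, equal variances and balanced cells. Only if both runs entered without a time term would the loss be severe. Severity: should fix.

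**What to change.** For each behavioural outcome of this task and for the social weighting parameter, name the post-stimulation value as the dependent variable. Enter the pre-stimulation value of the same measure as covariate, and diagnosis, stimulation and their interaction as factors. Where information type is kept in the model, test stimulation × information type on the baseline-adjusted scores; this addresses the claim that iTBS affects social but not non-social updating.

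Prefer this to adding time as a within-subject factor or analysing change. The two are not interchangeable: at r = 0.3 the stimulation × time test (44%) does worse than ignoring the baseline (57%), and at r = 0.5 it gains nothing.

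The cost is a change of wording in the analysis section. The pre-stimulation run is already planned, so no extra visits, participants or measurements are needed.
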